
Cognitive training programs often incorporate culturally tailored elements to enhance acceptability and engagement among participants. In practice, training materials delivered in English may be ineffective for individuals who do not understand the language. However, culturally matched cognitive training programs remain scarce in Chinese-speaking societies despite rapid demographic aging and the growing burden of dementia. Therefore, this study with Chinese cognitive training materials investigates whether this culture-match, structured cognitive training is related to outcomes in individuals with SCD and examines potential neurobiological and systemic correlates of any observed effects, such as blood inflammation marker (cortisol). Specifically, we propose to evaluate the impact of Chinese Classics recitation training through comprehensive multimodal assessments, including neuropsychological testing, functional magnetic resonance imaging (fMRI) (Rajah and D'Esposito, 2005; Anthony and Lin, 2018), electroencephalography (EEG) (Yu W. Y. et al., 2024), blood biomarker profiling (Teruya et al., 2021), and gut microbiota (Kuijer and Steenbergen, 2023) and fecal metabolomic analyses (Zhao et al., 2025). By integrating behavioral intervention with advanced neuroimaging and biomarker methodologies within a culturally grounded educational framework, this study seeks to address current gaps in the literature and provide population-specific evidence relevant to Chinese-speaking communities. Such an approach may contribute to the development of precision-oriented, low-risk intervention strategies for early cognitive decline in aging populations. We will primarily aim to evaluate the feasibility and acceptability of classical recitation training in older adults with subjective cognitive decline. As a secondary objective, we will investigate whether recitation training correlates with changes in neuroimaging markers associated with brain plasticity. Additionally, exploratory objectives include characterizing metabolomic and gut microbiota profiles and examining their potential associations with cognitive and neuroimaging outcomes. These exploratory analyses are designed to generate preliminary data and inform future hypothesis-driven research exploring potential pathways linking recitation training, gut-brain interactions, and neuroplasticity, representing a novel mechanistic framework.

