#### Clinical evaluations and laboratory testing

2.5.1

A structured research questionnaire will be administered to collect comprehensive baseline information, including age, biological sex, years of education, comorbidities, medication history, family history of neurodegenerative diseases, smoking and betel nut use, dietary preferences, eating habits, coffee or tea consumption (Zhang et al., 2026), bowel movement patterns, and prior experience with memorization training (e.g., structured memorization of Chinese Classics for more than 3 months). The questionnaire may be completed independently by participants or administered by trained research personnel. In addition to questionnaire-based assessments, participants will undergo basic physical examinations and detailed neurological evaluations.

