##### Statistical analysis

2.5.2.5

Statistical analyses will be conducted within the framework of the general linear model (GLM). For the primary clinical outcomes (e.g., subjective cognitive measures, neuropsychological test scores), a linear mixed-effects model will be used to handle the repeated-measures structure of the data throughout baseline, post-intervention, and follow-ups, with time, group, and group × time interaction as fixed effects, and subject as a random effect. This approach naturally accommodates missing data under the missing-at-random (MAR) assumption without requiring complete cases. The primary analysis will follow the intention-to-treat principle, including all randomized participants regardless of adherence or dropout, with missing values handled using multiple imputation based on baseline characteristics and available follow-up data. A per-protocol sensitivity analysis will also be conducted, restricted to participants who complete at least 80% of the intervention sessions. Covariates to be included in adjusted models will comprise age, sex, years of education, and baseline cognitive scores, selected *a priori* for their known associations with cognitive outcomes in SCD populations.

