### Statistical methods

2.6

The primary efficacy analysis will be conducted using generalized linear mixed-effects models to analyze repeated measures data, with adjustment for relevant covariates. Microbiome analyses will be performed using DESeq2 to identify differentially abundant taxa and linear discriminant analysis effect size to detect potential microbial biomarkers. Metabolomic data will be analyzed using partial least squares discriminant analysis, and pathway enrichment analysis will be conducted using the MetaboAnalyst platform. Multi-omics integration will be performed using Spearman correlation-based network analysis and causal mediation analysis to investigate regulatory mechanisms along the gut-brain axis. Multiple comparisons will be corrected using FDR, with a threshold of *q* < 0.05. All statistical analyses will be conducted using R (version 4.4.0; R Core Team, 2024) and SPSS (version 29.0; IBM Corp., Armonk, NY, USA), with statistical significance set at *p* < 0.05.

Given the inherent complexity and multi-layered nature of multi-omics data, if the aforementioned methods are insufficient for comprehensive analysis, we will collaborate with the institutional Artificial Intelligence Center affiliated in our hospital to implement advanced analytical approaches. These may include machine learning, network-based modeling, and partial least squares regression, among others, to construct predictive models that characterize causal or associative relationships between biological markers and clinical outcomes (e.g., cognitive function and depression). The predictive performance of different models will be systematically compared.

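### The Spearman network named for the gut–brain aim has no covariate set or compositional transform attached, so shared causes and 16S closure can produce edges

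*Protocol article*

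**What the plan says.** - **Objective (section 1, Introduction).** The exploratory aims include "characterizing metabolomic and gut microbiota profiles and examining their potential associations with cognitive and neuroimaging outcomes".
- **Method (section 2.6).** "Multi-omics integration will be performed using Spearman correlation-based network analysis and causal mediation analysis to investigate regulatory mechanisms along the gut-brain axis". The sentence gives no covariates, no transform, and no statement on whether arms are pooled.
- **Multiplicity (section 2.6).** "Multiple comparisons will be corrected using FDR, with a threshold of" q < 0.05.
- **Fallback (section 2.6).** If these methods fall short: "These may include machine learning, network-based modeling, and partial least squares regression, among others, to construct predictive models". Their purpose is to "characterize causal or associative relationships between biological markers and clinical outcomes".
- **Covariates (section 2.5.2.5).** "Covariates to be included in adjusted models will comprise age, sex, years of education, and baseline cognitive scores". This follows the description of the mixed model for clinical outcomes. Section 2.6 likewise mentions adjustment only for the efficacy mixed model.
- **Data collected (section 2.5.1).** The baseline questionnaire covers "dietary preferences, eating habits, coffee or tea consumption", together with bowel pattern, comorbidity and medication. No analysis is said to use them.
- **Microbiome (sections 2.5.5 and 2.6).** DESeq2 compares abundance between groups. No log-ratio step is tied to the correlations.
- **Status (section 3.3).** Gut microbiota and metabolomic measures are exploratory, not powered for confirmation, and meant in part to identify candidate biomarkers.

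**The concern.** An omics feature and a cognitive or imaging outcome are both measured after entry, and neither is randomised. Age, education or diet can move both. Section 2.5.2.5 itself justifies its covariates by their known relation to cognition, and sections 3.1 and 3.3 describe education as changing activation patterns. Ordinary Spearman correlation is bivariate, so carrying a covariate needs a different statistic, such as partial Spearman or rank regression. Mediation analysis does not escape the problem: randomisation protects the path from arm to mediator but not the path from mediator to outcome.

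The second issue concerns 16S abundances. They are relative, so a rise in one dominant taxon lowers the share of all the others. A real link between that taxon and an outcome then appears, with reversed sign, in taxa that have no link.

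FDR control is no remedy in principle. It limits the share of null correlations among the edges declared, and a confounded or closure-induced correlation is not null. What is at stake is which candidates are carried into later trials under a mechanistic label.

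**Working it through.** **The plan's own figure.** The only formal calculation (section 2.3) is d = 0.18, one-sided alpha 0.05, power 0.80, giving 383 per group. It reproduces: the exact noncentral t gives power 0.8006 at 383 and 0.7997 at 382. It does not concern the omics correlations, and is used below only as a benchmark for an arm effect.

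**Inputs.** n = 60 is from section 2.3. Some runs used n = 57, since 72 × 0.8 = 57.6. All correlations, loadings and taxon distributions are assumptions, because the article gives none.

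**1. Shared cause.** If one cause correlates r with both variables and there is no direct link, the induced Pearson correlation is r². For normal data the Spearman value is (6/π)·arcsin(r²/2). The approximate test statistic is z = atanh(ρ)·√((60 − 3)/1.06) = 7.333·atanh(ρ), compared with 1.96.

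| r | r² | Spearman ρ | z | P(p < 0.05), formula | Simulated, raw | Simulated, partial |
|---|---|---|---|---|---|---|
| 0.3 | 0.09 | 0.086 | 0.63 | about 10% | 9–10% | about 5% |
| 0.4 | 0.16 | 0.153 | 1.13 | about 20% | 21% | about 5% |
| 0.5 | 0.25 | 0.239 | 1.79 | about 43% | 45% | about 5% |

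**2. The same after FDR.** With 50 features, Benjamini–Hochberg at 0.05 and n = 57, the flagged share falls to about 0.5% at r = 0.3, 2–5% at 0.4 and 8–25% at 0.5. The fall comes from the stricter threshold; the bias is unchanged.

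**3. Pooling the arms.** If training shifts both variables by d, the induced correlation is (d²/4)/(1 + d²/4).
- d = 0.18: 0.0081/1.0081 = 0.008; false edges 5.5%.
- d = 0.5: 0.0625/1.0625 = 0.059; 7.3%.
- d = 0.8: 0.16/1.16 = 0.138; 17.8%.

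Adjusting for arm returns all three to 5.1–5.4%.

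**4. Closure, 16S relative abundances only.** There are 50 log-normal taxa, one of them dominant, and the outcome is linked to the dominant taxon only. Entries are the share of unlinked taxa with p < 0.05.

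| Setting | Proportions | Centred log-ratio |
|---|---|---|
| n = 60, no taxon linked | 4.9% | 4.7% |
| n = 60, link 0.3 | 11.4% | 4.9% |
| n = 60, link 0.5 | 16.6% | 5.2% |
| n = 57, dominant share 0.2–0.4, link 0.3–0.5 | 6.6–20.5% | 4.1–5.5% |

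In the n = 57 setting, FDR brings the share on proportions down to 0.3–5%. Taxon–taxon edges with no true link (n = 60, no taxon linked to the outcome) appear in 19.3% of tests on proportions and 5.3% after the transform.

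**5. Price of adjustment.** At n = 60 the correlation detectable with 80% power is about 0.364, and atanh(0.364) ≈ 0.382. With k covariates, power is Φ(0.382·√((57 − k)/1.06) − 1.96).
- k = 0: 80%.
- k = 4: Φ(2.70 − 1.96) ≈ 77%.
- k = 10: Φ(2.54 − 1.96) ≈ 72%.

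**The case against.** The strongest reply is that the article is silent. A reader might infer that the correlations will be run raw, pooled and unadjusted. No sentence says so, and a condensed article may leave the covariate set and preprocessing to a full protocol or analysis plan that is not shown. That stands. What remains is that the article names a bivariate statistic for a mechanistic purpose and ties its covariates to a different model.

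Other points that stand:
- Section 2.6 assigns the network to multi-omics integration and does not say that cognition or imaging are nodes. That link is inferred from the objective in the Introduction.
- Spearman is not the only method. Mediation analysis is in the same sentence, and its outcome model would normally contain arm.
- Per-test rates are not rates under the planned FDR, which lowers them substantially.
- Stable traits tend to correlate less with changes than with levels, so shared-cause correlations of 0.4 to 0.5 are harsh if changes are analysed.
- Arm pooling is negligible at the document's d = 0.18.
- Closure does not create taxon–outcome links where none exist, and it does not apply to the targeted metabolites or the Shannon index.
- Adjusting for arm also removes covariation that training itself produces, which is part of what the study wants to see.

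A reader might also infer that artefacts will be published as established gut–brain links. The documents do not support that: the objective speaks of potential associations, and section 3.3 makes these outcomes exploratory with descriptive reporting. This does not fully dispose of the point, because the same measures are meant to select candidate biomarkers and section 2.6 sets significance thresholds for them.

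**Conclusion.** The point holds in a limited form. Section 2.6 fixes a Spearman network and mediation analysis for a mechanistic aim without attaching a covariate set or a compositional transform, although relevant baseline data are collected. Under assumed shared-cause correlations of 0.3 to 0.5, about 9% to 45% of single tests at n = 60 give a false edge, against about 5% with partial Spearman. After FDR the problem is small at 0.3 and still material at 0.5. Closure in 16S abundances gives about 7% to 21% per test against about 5%, provided a dominant taxon truly relates to the outcome. The direction is certain; the size depends on correlations that the article does not report. Because the outcomes are exploratory, this is a low-cost improvement to candidate selection and not an error in a confirmatory result.

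**What to change.** In section 2.6:
1. Apply a centred log-ratio transform to the 16S abundances before any correlation, with a stated rule for zeros.
2. Use partial Spearman or rank regression, adjusted for age, sex and years of education, plus a small diet and bowel summary chosen in advance.
3. Show edges with and without adjustment for arm, and say which question each version answers.
4. Use the same baseline covariates in the mediator–outcome models.
5. Describe unadjusted edges as descriptive associations.

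**Cost.** Wording and a few lines of code, with no new data. Each covariate uses a degree of freedom: about 3 points of power with four, about 8 with ten. Diet and bowel items with many categories would use more, so the set should stay short.

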## Methods and analysis

2

### Aims, study design, and settings

2.1

This study aims to estimate preliminary effect sizes to inform sample sizes for future definitive trials, evaluate the feasibility and acceptability of memorization practice and multimodal assessments, and generate mechanistic hypotheses about the relationship among recitation practice, neuroimaging biomarkers, and gut-brain axis markers, particularly for individuals with SCD. By analyzing changes in fMRI, neuropsychological assessments, and physiological biomarkers, including blood sampling, plasma metabolomic profiling, and fecal microbiota and metabolomic analyses, we seek to elucidate both the short-term practicability of structured recitation training and its underlying neurobiological mechanisms in SCD. Regarding long-term implications, our database will primarily consist of Chinese-speaking Asian participants. The longitudinal follow-up data will enable a more comprehensive understanding of the progression of SCD within this specific population, thereby addressing an underrepresented demographic in current SCD research.

The study is designed as a randomized, assessor-blinded, controlled pilot study. A stratified block randomization sequence will be generated by an independent statistician using computer-generated random numbers, with stratification by age and sex to ensure balanced group allocation. Block sizes will be randomly varied to prevent predicting upcoming assignments. Allocation concealment will be ensured using the Sequentially Numbered, Opaque, Sealed Envelopes method; envelopes will be prepared and safeguarded by personnel not involved in recruitment, eligibility assessment, or intervention delivery. After eligibility assessment and informed consent are completed, a designated research assistant — otherwise uninvolved in outcome assessment — will open the envelope to reveal group assignment. Prior to allocation disclosure, all research personnel will remain blinded to the randomization sequence. Given that the intervention is behavioral in nature, complete blinding of participants and interventionists is not feasible. However, several measures will be implemented to minimize performance bias. Participants will be instructed not to discuss their group assignment with outcome assessors. Interventionists will have no role in outcome measurement or data analysis. Outcome assessors — including neuropsychological evaluators (psychologists) and radiologic technologists — will be formally blinded to group allocation throughout the trial and will be kept separate from the intervention team. To maintain blinding integrity, assessors will be reminded of their blinded status at each assessment visit, and any unblinding events will be documented and reported. Data analysts will similarly remain blinded to group assignment until the primary analysis is complete. The inherent risk of performance bias arising from participant awareness of group assignment will be mitigated by standardizing intervention protocols, using objective outcome measures where possible, and monitoring for differential dropout between groups.

Participants will be randomly assigned to either an intervention group or a non-active control group (Figure 1). This design decision is informed by a meta-analysis conducted by Bhome et al., which reported that cognitive training interventions in SCD demonstrated statistically significant improvements primarily when compared with non-active control conditions. In contrast, comparisons with active control groups receiving alternative forms of cognitive stimulation (e.g., watching educational films) did not yield statistically significant differences (Bhome et al., 2018). The absence of an active control group, a cognitive placebo condition, a social interaction control group, and a Hawthorne effect control group represents a recognized limitation of the present design. However, the decision to use a non-active control was made to maximize detection sensitivity in this pilot study, consistent with prior literature (Bhome et al., 2018). Future definitive trials should incorporate an active control condition matched for time, social contact, and participant engagement to permit more rigorous causal interference.

**Figure 1 fig1:**
[figure not shown]
Workflow of the randomized controlled trial. This flowchart illustrates the recruitment, screening, and enrollment process for participants. aMIC, abbreviated Memory Inventory for the Chinese; OPD, outpatient department; SCD, subjective cognitive decline.

The intervention group will undergo structured memorization training through recitation of Chinese Classics for 6 months. The intervention will be delivered by trained research assistants in weekly 60-min sessions, supplemented by approximately 10 min of individual daily practice over the six-month period. The control group will not receive memorization training during this period. To ensure reproducibility, a detailed intervention manual has been developed specifying recitation materials, progression criteria, and instructor guidance. All instructors will complete a standardized training program prior to the commencement of the study, encompassing both the theoretical rationale for the intervention and practical delivery skills. Instructor competency will be formally assessed before authorization to deliver sessions. As this study is conducted at a single center — China Medical University Hospital — inter-center standardization is not applicable to the current protocol; however, the intervention manual will be designed to support multi-site replication in future trials.

Intervention fidelity will be monitored through the following method. Daily home practice will be tracked via automated logs within the mobile application, capturing login frequency, session duration, and task completion rates. Adherence will be operationally defined as completion of at least 80% of the designated training, including at a minimum of 80% of scheduled training sessions and the fulfillment of at least 80% of the assigned daily practice throughout the six-month duration. Participants falling below this threshold at any monthly review will be contacted by the research team to identify and address barriers to engagement.

Following completion of the initial six-month intervention phase, participants will be given the option to voluntarily continue recitation practice. The selection of a six-month intervention period is informed by the MEMO+ (Méthode d’Entrainement pour Mémoire Optimale) protocol developed by Sylvie Belleville and colleagues (Bier et al., 2015). Later studies from the same research team have demonstrated that participants receiving structured cognitive training exhibited significant improvements in memory recall performance, with effects persisting for at least 6 months post-intervention (Belleville et al., 2018). Furthermore, long-term follow-up over 5 years revealed that individuals who had undergone cognitive training experienced a slower decline in delayed memory performance and Montreal Cognitive Assessment (MoCA) scores compared with control groups (Belleville et al., 2024). These findings underscore the sustained benefits and potential long-term impact of continuous cognitive training.

Additional support for the selected intervention duration is derived from studies examining other forms of cognitively engaging activities. For example, interventions involving structured calligraphy practice have demonstrated that extending training duration over a six-month period leads to significant alterations in functional brain connectivity (Lee et al., 2024). Specifically, increased connectivity has been observed between the medial prefrontal cortex (mPFC) and right lateral temporal cortex (LTC), mPFC and right inferior parietal lobe (IPL), left hippocampal formation (HF) and right LTC, as well as between the left HF and right IPL (Lee et al., 2024). These findings suggest that prolonged engagement (6 months) in cognitively demanding tasks may induce measurable neuro-modulatory effects at the network level.

Taken together, a 6-month intervention period represents a balanced design choice: it is sufficiently long to allow for detectable behavioral and neurobiological changes, yet not so prolonged as to compromise participant adherence. Accordingly, outcome assessments will be conducted at baseline (time of recruitment), immediately after the six-month intervention, and at one-year and two-year follow-ups, with annual assessments thereafter until participants are no longer able to complete evaluations. The study will be conducted at China Medical University Hospital, primarily within the outpatient clinics of the Departments of Neurology or Psychiatry.

